**1. ABSTRACT**

In view of the low breastfeeding rates (BF) and practical sub-optimal complementary feeding in Brazil; the large number of adolescent mothers in our country; the presumed influence of grandmothers on feeding practices of their grandchildren; the fact that adolescent mothers who live with their mothers (maternal grandmothers of children) are considered to have an increased risk of inadequate feeding practices of their young children; and also the lack of intervention studies with adolescent mothers and grandmothers, it was conducted in the years 2006 to 2008, a randomized clinical trial to evaluate the efficacy of an intervention (six BF counseling sessions and healthy complementary feeding, carried out in the first four months of the child's life, the first in the maternity and the others in households) directed to adolescent mothers and grandmothers on exclusive breastfeeding prevalence (EBF) in the first six months of life and the BF prevalence and adoption of healthy complementary feeding and timely in the first year of life. Due to the favorable results of the intervention on all outcomes studied, it is intended, with this study, knowing the impact of the intervention on dietary habits and nutritional status of children in preschool age and brothers who are born after the intervention. For this, 252 children who were part of the clinical trial will be reassessed at age 4-6 years and younger siblings. Children in the intervention group will be compared with the control group regarding: anthropometric indicators (BMI, height), diet, adequacy of intake of macro and micronutrients as recommended for the age group (Dietary Reference Intakes - DRIs), the duration of BF (preschool for only), the duration of EBF and BF prevalences in the first year of life (only for younger siblings). To quantify the impact of the intervention in the various outcomes will be used Cox regression (hazard-ratio). In the analyzes, will be considered cohabitation with the grandmothers and other relevant variables. Our hypothesis is that the positive impact of the intervention acquired in the first year of life has positively reflected in anthropometric indicators and eating habits of children in preschool and younger siblings.

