- The intervention reduced the unnecessary use of water and / or teas in children breastfed for the first six months by 52% (HR = 0.48, 95% CI 0.31 to 0.76) when it was applied only to adolescent mothers. When the intervention included maternal grandmothers, the protection was 47% (HR = 0.53; CI 95% = 0.35-0.80); and postponed for 44 days the use of these liquids in the group where only the adolescents received the intervention (78 days, 95% CI 50.2 to 105.8 without intervention versus 122 days, 95% CI 107.6 to 136.3 with intervention) and 67 days in the group where the grandmothers were also included in the intervention (63 days, 95% CI 47.2 to 78.7 without intervention versus 130 days, 95% CI 113.4 to 146.6 with intervention29.
- The intervention increased the median duration of EBF in 67 days in the group that only adolescent mothers received the intervention (103 days; 95% CI = 82.4 to 123.5 with intervention versus 36 days; 95% CI = 21.5 to 50 5 without intervention) and 46 days in the group where the grandmothers were also included in the intervention (89 days, 95% CI 56.8 to 121.2 with intervention versus 43 days, 95% CI 29.9 to 56.1 without intervention); and reduced by 48% the EBF abandonment in the first half when applied only to adolescent mothers (HR = 0.52; 95% CI = 0.36-0.76) and 36% when included maternal grandmothers (HR = 0,64, 95% CI = 0.46-0.90)30.
- The probability of a child be fed with another milk remained lower over the first six months of life in the group receiving the intervention. The median age of introduction of other types of milk was 95 days (95% CI 78.7 to 111.3) in the control group and 153 days (95% CI 114.6 to 191.4) in the intervention group. Therefore, the intervention delayed in nearly two months the introduction of other milks31.
- The intervention had a positive impact on the early introduction of complementary foods. At four months, 41% (95% CI 32.8 to 49.2) of the control group were receiving complementary foods. This prevalence decreased to 22.8% (95% CI 15.9 to 29.7) in the intervention group. However, the six-month prevalence rates of children receiving complementary foods were similar in both groups: 88.4% (95% CI 82.9 to 93.9) for the control group and 87.1% (95% CI 81,4 to 92.8) in the intervention group31.

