**5.2 Methodology of the second phase (current project) study**

Phone contacts will be made with mothers / families to invite the children involved in the first phase of the trial and his younger brothers, when present, to participate in the second phase of the project and request that attend the Clinical Research of the Hospital de Clínicas de Porto Alegre in pre-defined date. Mothers / families who are not found by phone will be visited at home.

Data collection will take place at the Clinical Research Center of the Hospital de Clínicas de Porto Alegre or at home with semi-structured questionnaire to obtain information on the current socio-demographic characteristics and some aspects related to the frequency of children in school preschool or day care; food frequency questionnaire to investigate the consumption of food (the same applied in the first phase of the study) and anthropometric measurements of children.

For the anthropometric measurements of children, will be taken two weight measures with the child barefoot wearing light clothing, positioned in the center of the scale (portable electronic scale with capacity of up to 200kg and sensitivity 50g), upright and distributed weight on both feet; and two height measurements with the barefoot child, standing upright, positioned in the center of the product, with arms extended along the body and the head up, looking at a fixed point at eye level. The heels, shoulders and buttocks should be flat on the stadiometer and internal bones of heels must touch as well as the inside of the knees, and feet must be united making a right angle to the legs. Will be calculated body mass index (BMI = weight [kg] / height2) and for the classification of children as the BMI / age and height / age will be used the new curves and WHO parameters35-37.

Data collection and anthropometric measurements will be performed by three students graduate, which will remain blinded to the groups they belong to children and their siblings (experimental or control).

The data collected will be stored by double entry, using the Excel program. For statistical analysis, SPSS for Windows is used.

Statistical analyzes will be based on the principle of "intention to treat". Initially, key features will be compared of patients lost to follow-up on those who are evaluated to rule out possible selection bias. The following comparisons of preschool and younger children in the intervention group with the control group will be made:

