- Anthropometric indicators (BMI, height) using mean z scores nutritional classification of children.
- Eating habits, using the data to be obtained from the food frequency questionnaire. You may also be compared to the adequacy of diet in the first year of life with current.
- Following the 10 steps of healthy eating for children 2-10 years using the data to be obtained from the food frequency questionnaire.
- Adequacy of macro and micronutrients intake as recommended for the age group (Dietary Reference Intakes - DRIs).
- Total duration of breastfeeding (preschoolers only), using medians.
- Duration of EBF, prevalence of BF and adoption of healthy complementary feeding in the first year of life (for the younger siblings of preschoolers).

To quantify the impact of the intervention in different outcomes, the hazard ratios (HR) and 95% confidence intervals will be calculated by means of Cox regression. In the analyzes, will be considered cohabitation with the grandmothers and other relevant characteristics . Will be adopted p <0.05 as level of statistical significance.

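### Cox hazard ratios are the only effect measure named for all outcomes, yet BMI, height, current diet and nutrient adequacy are status at one assessment with no event time

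*Protocol*

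**What the plan says.** Section 5.2 lists six comparisons between the randomised groups: anthropometry, eating habits, the ten steps of healthy eating, adequacy of macro- and micronutrient intake against the DRIs, total BF duration of the preschoolers, and, for younger siblings, EBF duration with BF prevalence and complementary feeding. The first is worded "Anthropometric indicators (BMI, height) using mean z scores nutritional classification of children" and the second "Eating habits, using the data to be obtained from the food frequency questionnaire". Medians are named for total BF duration.

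The sentence after the list gives the only effect measure and the only confidence interval in the plan: "To quantify the impact of the intervention in different outcomes, the hazard ratios (HR) and 95% confidence intervals will be calculated by means of Cox". Adjustment for cohabitation with the grandmother and other characteristics follows directly. The abstract repeats the rule after a list that opens with BMI, height and diet: "To quantify the impact of the intervention in the various outcomes will be used Cox regression (hazard-ratio").

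Section 5.2 describes one second-phase data collection, consisting of a questionnaire, a food frequency questionnaire, and weight and height. The wording "will be taken two weight measures with the child barefoot wearing light clothing", with two height readings as well, describes duplicate readings at that assessment and not follow-up.

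**The concern.** A hazard ratio needs an event and a time at which it occurs. Weaning and the end of exclusive breastfeeding have both. A BMI-for-age z-score at age 4 to 7 has neither, and being overweight or having an inadequate intake on the day of the visit is a state whose onset was not observed.

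The general aim is dietary habits and nutritional status, and the Hypothesis section names BMI, height, eating habits and nutrient intake among the main outcomes. For these outcomes the plan names an effect measure that cannot be computed, or that can be computed only through a device it does not describe. An analyst who follows it must either depart from the protocol or choose an artificial time variable, and different choices give different answers.

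**Working it through.** **1. Which listed outcomes have an event time**

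| Outcome in section 5.2 | Type | Hazard ratio meaningful? |
|---|---|---|
| BMI and height z-scores | continuous, one assessment | no |
| Nutritional classification | category, one assessment | no |
| Eating habits, ten steps | current status from the questionnaire | no |
| DRI adequacy | current status or intake level | no |
| Total BF duration, preschoolers | duration | yes |
| EBF duration, siblings | duration | yes |
| BF prevalence, siblings | proportion | no |

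The food frequency questionnaire was also used in the first phase, and section 5.2 allows a comparison with first-year diet. A second reading does not create an event time.

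**2. Continuous z-scores.** With no event, there is no hazard and so no hazard ratio. No number can repair this.

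**3. Yes/no status, Cox with the same time for everyone.** Let a and c be the numbers with the outcome among n1 and n0 children. With a single event time and Breslow ties, the estimate is (a/n1)/(c/n0), a prevalence ratio. The information is ac/(a+c), so:

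- model-based variance of the log ratio: 1/a + 1/c
- binomial variance of the log ratio: 1/a − 1/n1 + 1/c − 1/n0

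With equal arms and equal prevalence p, the first divided by the second is 1/(1−p). The standard error is therefore inflated by 1/√(1−p), and the true size of a nominal two-sided 5% test is 2{1 − Φ(1.96/√(1−p))}. Neither depends on sample size. The prevalences below are assumptions, because the protocol gives none for this population.

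| Assumed p | SE inflation | True two-sided size |
|---|---|---|
| 10% | 1.05 | 3.9% |
| 30% | 1.20 | 1.9% |
| 50% | 1.41 | 0.6% |
| 70% | 1.83 | 0.03% |

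A simulation at 30% (1,500 replicates) gave a size of 2.3%, in line with 1.9%.

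The Introduction cites preschool overweight of 3.8% and 11.8% in a Japanese cross-sectional study. At those values the inflation is 1/√0.962 = 1.02 and 1/√0.882 = 1.06, and the size about 4.6% and 3.7%. For an outcome that rare the error is small.

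**4. Worked example (assumed counts).** Take 252 children split 126 per arm with no losses, and 38 against 50 with the outcome. The ratio is 38/50 = 0.76.

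- Constant-time Cox: SE = √(1/38 + 1/50) = 0.215, 95% CI 0.50 to 1.16.
- Binomial: SE = √(1/38 + 1/50 − 2/126) = 0.174, 95% CI 0.54 to 1.07.

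**5. Power illustration (assumed 60% against 42%, 126 per arm, no losses).** The log ratio is ln(0.42/0.60) = −0.357.

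- Binomial SE = √[(0.40/0.60 + 0.58/0.42)/126] = 0.1275, and power = Φ(0.357/0.1275 − 1.96) ≈ 80%.
- Cox SE = √[(1/0.60 + 1/0.42)/126] = 0.1792, so rejection needs a log ratio beyond 1.96 × 0.1792 = 0.351. Power = Φ((0.357 − 0.351)/0.1275) ≈ 52%.

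This is one scenario at a high prevalence. At low prevalence the loss is slight.

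**6. Yes/no status, Cox with age at visit as time.** This treats the visit date as the onset date. Simulation assumptions: 30% prevalence in both arms, ages spread evenly over 3 years, 126 per arm, 300 replicates. Mean age gaps between arms of 0, 0.25 and 0.5 years gave median hazard ratios of 0.97, 0.69 and 0.51, although prevalence did not differ. The gaps are assumptions. Randomisation should keep them small unless the arms are seen at different times.

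**The case against.** The case on the other side has real parts.

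- **The protocol does not literally say every outcome.** That is correct, and Cox is right for two of the listed outcomes. But the sentence closes the whole list, the abstract agrees with it, and no other effect measure is named.
- **Mean z-scores are planned for anthropometry.** This stands. A reader might infer that the plan offers no valid comparison for BMI and height. It does: comparing mean z-scores between randomised groups is sound. What is missing is a matching effect estimate with an interval, and the adjustment is attached only to the Cox sentence.
- **Variance is a matter for the SAP, and constant-time Cox with robust variance is valid.** This also stands. The protocol mentions neither constant time nor a variance type, so the figures in steps 3 to 5 apply only to the model-based version. Even with robust variance the result is a prevalence ratio, not a hazard ratio, and the z-scores remain uncovered. Nor is this an omission that an SAP would fill: it would have to override what the protocol states.
- **The interval error is conservative.** True for constant-time Cox. A reader might infer a risk of false positive findings from this variance; the risk is of missing a real effect.

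A reader might also infer that Cox fails for the feeding durations, because the Introduction reports complementary feeding of 41% against 22.8% at four months, while "the six-month prevalence rates of children receiving complementary foods were similar in both groups" (88.4% and 87.1%). Those figures imply a hazard ratio of about ln(0.772)/ln(0.59) = 0.49 up to four months and [ln(0.772) − ln(0.129)]/[ln(0.59) − ln(0.116)] = 1.10 from four to six. They concern first-phase introduction of complementary foods. They say nothing about total BF duration of the preschoolers or EBF duration of the siblings, so the documents do not support that inference.

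**Conclusion.** The point holds. As written, the protocol names Cox hazard ratios as the sole effect measure with an interval for a list made up mostly of outcomes without an event time. For the z-scores the measure is undefined, and this rests on no assumption. For yes/no outcomes the consequence depends on how Cox is run:

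- **Constant time, model-based variance:** standard errors 1.05 to 1.83 times too large over assumed prevalences of 10% to 70%, and only 1.02 to 1.06 times at the overweight prevalences cited in the Introduction. The error is conservative.
- **Constant time, robust variance:** valid, but it estimates a prevalence ratio.
- **Age at visit as time:** an uninterpretable onset time, and an estimate that moves with any age gap between arms.

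Total BF duration and sibling EBF duration are correctly served by Cox, and the comparison of mean z-scores is valid as far as it goes. No bias in that comparison is shown. All prevalences, the equal split of 252, the absence of losses, the 60% against 42% example and the age gaps are assumptions.

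**What to change.** Change the Cox sentence in section 5.2 and its counterpart in the abstract so that they state:

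- **Total BF duration (preschoolers) and EBF duration (siblings):** Kaplan-Meier and Cox regression, with hazard ratios and 95% CIs.
- **BMI-for-age z, height-for-age z and continuous intakes:** mean difference with 95% CI from linear regression, adjusted for the cohabitation stratum.
- **Yes/no outcomes (nutritional classification, DRI adequacy, ten steps, consumption of specified foods, BF prevalence in siblings):** prevalence ratio or difference with 95% CI from log-binomial regression or Poisson regression with robust variance. Constant-time Cox with robust variance is acceptable if the result is labelled a prevalence ratio.

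The cost is two sentences. No new data, visits or participants are needed, and the models are standard.

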**6. ETHICS CONSIDERATIONS**

This is a study with minimal risk to participants, according to the Research Rules Health (Decree 01/88 of the National Health Congress). Mothers or guardians will be informed about the study and only participate after signing written consent. Will be guaranteed the anonymity of participants and the use of results only for research purposes. The search will start after approval by the Scientific Committee of the Hospital de Clínicas de Porto Alegre. The clinical trial was registered at ClinicalTrials.gov, with the number NCT00910377.

Caretakers will be informed of the results of the assessment and, if necessary, will be advised to seek a health care facility.

**7. SCHEDULE**

| **Data** | **Activity** |
| --- | --- |
| March-June 2012 | Team Training |
| July 2012-April 2013 | Data collection - field work  Double data entry |
| May-June 2013 | Completion of data entry |
| July – October 2013 | Data analysis  Writing, translation and article submission |
| November – december 2013 | Defense of the Master's dissertations |
| January 2014 | Defense of the PHD thesis |

